**Objective:**

The primary objective of the Essential Fats for Enhancing Cognitive Thinking study is to determine the impact of walnuts on postprandial cognitive function in adults with SCI. Secondary objectives include assessing the impact of daily walnut consumption for 1 week on cognitive function and erythrocyte fatty acids. Exploratory objectives include understanding the effect of walnut consumption on microbiota and intestinal inflammation.

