### Sample Size

The primary outcome used in sample size calculation was the postprandial cognitive test score from the NIHTB-CB. Based on our previous study [22], we obtained the SD (11.0) of the difference in postprandial cognitive test score between the unsaturated fat meal and the saturated fat meal. We had 80% power with 78 participants to detect a difference of 3.5 in postprandial cognitive test score between the control and the walnut group using a 2-sided paired *t* test with a type I error of 0.05.

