A linear mixed effect model with subject-specific random intercept will be fit on the change of endotoxemia during the 7-day intervention with the following covariates: study group, BMI, age, sex, and education level. The regression coefficient of this study’s group will be the adjusted difference in the reduction of endotoxemia between this study’s groups. β*-*diversity of the microbiome community at days 7 and 42 between all pairs of participants will be calculated using the Bray-Curtis dissimilarity measure. Nonmetric multidimensional scaling ordination will be computed, and nonmetric multidimensional scaling plots will be generated to visualize the difference in β-diversity between study groups. Permutation-based ANOVA will be used to compare the β-diversity between study groups. Operational taxonomic units (OTU) abundance will be compared between study groups using paired *t* tests for each OTU, and the *P* values will be adjusted by the Benjamini-Hochberg procedure [76] to control for false discovery rate. A linear mixed effect model with subject-specific random intercept will be fit on postprandial test score with the following covariates: change of endotoxemia during the 7-day intervention, change of OTU abundance during the 7-day intervention, BMI, age, sex, and education level. As the number of OTUs will be very large, exceeding the sample size, a LASSO (Least Absolute Shrinkage and Selection Operator) penalty [77] will be included in the regression model to select significant covariates.

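### LASSO selection of OTUs is described as selecting significant covariates, but selection controls no error rate, and the Benjamini-Hochberg step covers only a different OTU analysis

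*Protocol article*

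**What the plan says.** The Statistical Analysis section of the protocol article plans two different analyses of OTUs.

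- **Between-group comparison.** Each OTU is compared between study groups with a paired t test, and the P values "will be adjusted by the Benjamini-Hochberg procedure" for false discovery rate control.
- **Link to cognition.** A mixed model with a random intercept per participant is fitted to the postprandial score. Its predictors are the change in endotoxemia together with "change of OTU abundance during the 7-day intervention, BMI, age, sex, and education level". The reason given for penalising is: "As the number of OTUs will be very large, exceeding the sample size". The LASSO penalty "will be included in the regression model to select significant covariates".

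For the second analysis the article states no test, P value or multiplicity adjustment. The abstract places the microbiota work at the lowest tier: "Exploratory objectives include understanding the effect of walnut consumption on microbiota and intestinal inflammation".

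**The concern.** The sentence makes selection by LASSO the route to significance. LASSO minimises a penalised loss. Whether a coefficient is non-zero depends on the penalty value, and the usual ways of choosing that value aim at prediction error or an information criterion, not at a false-positive rate.

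The authors recognise multiplicity across OTUs, because they control the false discovery rate in the between-group comparison. The cognition model draws on the same large OTU set, and there the only stated criterion is the penalty. A reader of the results would meet significant OTUs from both analyses and could not tell that only one list has error control. The Discussion (Comparison With Prior Work) says the relationship between gut microbiota and postprandial cognition will be examined, so this list will be interpreted.

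**Working it through.** **1. The plan's own figure.** The article gives no figure for the LASSO step. The only related figure is the sample size, which fixes how many participants the model has. Inputs from Sample Size: "we obtained the SD (11.0) of the difference in postprandial cognitive test score"; "We had 80% power with 78 participants to detect a difference of 3.5"; a two-sided paired t "test with a type I error of 0.05".

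n = (SD × (z₀.₉₇₅ + z₀.₈₀) / difference)² = (11.0 × (1.960 + 0.842) / 3.5)² = 77.5, rounded up to 78.

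The stated 78 is reproduced. Exact paired-t power at 78 is 79.2%, close to the stated 80%. With two periods each, the model has at most 78 × 2 = 156 records.

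**2. What error control would mean here.** Suppose no OTU is related to the outcome. Any selected OTU is then false, so the false discovery proportion is 1 whenever something is selected and 0 otherwise. The false discovery rate therefore equals the probability of selecting at least one OTU. A procedure controlling the false discovery rate at 5% would hold this probability to 5%.

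**3. Simulation under that null.** There were 300 datasets per scenario. The Monte Carlo standard error near 50% is √(0.5 × 0.5 / 300) = 2.9 percentage points.

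- From the documents: 78 participants, two periods, a random intercept, endotoxemia change and clinical covariates in the model, more OTUs than participants.
- Assumed, because the article does not give them: 200, 500 or 1000 OTUs; normally distributed OTU changes; intraclass correlation 0.5, treated as known; endotoxemia and clinical covariates unpenalised; the tuning rule.
- Tuning rules compared: 10-fold cross-validation by participant at minimum error, the same with the one-standard-error (1-SE) rule, BIC and AIC. BIC and AIC were limited to fits with fewer than 156 / 2 = 78 selected OTUs.

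Share of null datasets with at least one OTU selected:

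| Tuning rule | 200 OTUs | 500 OTUs | 1000 OTUs |
|---|---|---|---|
| Minimum cross-validation error | 43.7% | 55.3% | 60.7% |
| 1-SE rule | 1.3% | 3.0% | 9.7% |
| BIC | 5.0% | 6.7% | 5.7% |
| AIC | 89.7% | 96.0% | 97.3% |

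When minimum-error cross-validation selected anything, the median number of OTUs was 5, 7 and 13.5 respectively.

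**4. Sensitivity under minimum-error cross-validation.** With 500 OTUs correlated in blocks the share was 50.0%. With 500 OTUs, intraclass correlation 0.7 and the random intercept ignored, it was 61.3%. A separate run of 60 datasets with 200 OTUs gave 53%, and 0% under both the 1-SE rule and BIC. With so few datasets, this agrees with the table.

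**5. Reading.** With data generated in the same way, the false-selection rate runs from about 1% to 97% according to the tuning rule and OTU count. Values near 5% under BIC are a by-product of that criterion in these settings, not a level that anyone set.

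**The case against.** The strongest reply is that this turns on one word. Significant may loosely mean important or non-zero. Where the section plans formal testing it names P values and Benjamini-Hochberg, which suggests that the authors regard LASSO as dimension reduction. The article promises no P value for this model, and a full analysis plan may add post-selection inference. The work is exploratory.

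Part of this stands. Exploratory status limits the consequences, and the absence of a tuning rule or OTU count from a condensed article is no fault. But the objection here is to what is stated, not to what is missing. Naming a common tuning rule in an analysis plan would not turn selection into a significance test. Exploratory status justifies a candidate list but does not justify calling it significant.

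Two stronger readings are tempting, and the document does not support them.

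- A reader might infer that the plan will pick unrelated OTUs in about half of null datasets. That rate belongs to minimum-error cross-validation, which the article does not specify. Other common rules give very different rates.
- A reader might infer that endotoxemia, BMI, age, sex and education are penalised and may drop out of the model. The text says a penalty enters the regression model and gives the number of OTUs as the reason. It does not say which coefficients are penalised, and leaving the adjustment terms unpenalised is compatible with it.

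**Conclusion.** The point holds as a misstatement of what LASSO selection establishes. Followed as written, the rule attaches the label significant to OTUs with no type I error or false discovery control, beside an analysis in the same section that does have such control.

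Its size is conditional. For 200 to 1000 OTUs under a global null, the chance of at least one false selection is about 44% to 61% with minimum-error cross-validation, 1% to 10% with the 1-SE rule, 5% to 7% with BIC and 90% to 97% with AIC. These figures rest on the assumed OTU counts, normal data and an intraclass correlation of 0.5, and none of them is a property that the article fixes.

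The consequence is minor: it changes what an exploratory analysis can conclude. The primary paired comparison and the sample size of 78 are not affected.

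**What to change.** Reword the sentence so that the LASSO step yields a list of *selected* OTUs, described as exploratory candidates, and drop the word *significant*.

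If the authors wish to state that an OTU is associated with postprandial cognition, name one error-controlled procedure before the data are analysed and reserve the statement for OTUs that pass it. Two suitable choices are:

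- stability selection with a stated error bound; or
- a participant-level permutation test for each OTU, with Benjamini-Hochberg at 5% across OTUs.

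The rewording alone cures the misstatement. The second step is needed only if associations are to be claimed. The cost is more computing and probably fewer claimed OTUs. No new data are needed, and the primary analysis does not change.

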### Ethical Considerations

Review and approval for this study and all procedures were obtained from the OSU Institutional Review Board on April 24, 2023 (2023H0111). All interested potential participants were provided verbal and written information about this study, including a copy of the consent form. Potential participants had the opportunity to ask questions and be provided as much time as necessary to review the consent form and consider participating. Informed consent was obtained from all participants. Participants were compensated up to US $200 for participation in this study, where those who discontinued early received a prorated amount. Efforts were made to protect the privacy of this study’s participants, such as deidentifying participant information and limiting interactions with participants to essential study team members.

## Results

The EFFECT study was funded in May 2023. Recruitment began in February 2024, and the final study visits were projected to be completed in July 2025.

## Discussion

### Comparison With Prior Work

Studies examining cognitive function after consumption of a meal are limited. Fewer still are reports on the impact dietary fat has on postprandial cognitive function [22-24,28]. Of those investigations, comparisons have been made between a saturated fat meal and an unsaturated fat meal [22,23]. The unsaturated fat meals used dietary oils that were mostly composed of monounsaturated fat. In a population of women, the high saturated fat meal had a negative impact on cognitive function compared to the high unsaturated fat meal [22]. In a population of men, the negative impacts of the high saturated fat meal were only observed in men who were obese [23]. In contrast, the EFFECT study did not use dietary oils and instead used walnuts to deliver the unsaturated fat, included both men and women, and included anyone with a BMI over 20.

Delivering unsaturated fats and polyphenols through nuts instead of oil is not novel. A meal supplemented with almonds has also been investigated [24]. This meal was compared to a high-carbohydrate meal, which found that the high-fat almond meal ameliorated declines in cognitive function 2 hours after the meal. Most of the fat in almonds is monounsaturated fat. Differing from almonds, walnuts contain a higher proportion of polyunsaturated fats. Of note are ALA and LA, the 2 essential polyunsaturated fatty acids that cannot be synthesized and therefore must come from the diet. Walnuts are a rich source of both ALA and LA, whereas almonds contain no ALA and only a fraction of the LA that is present in walnuts. The unique fat composition and polyphenols of walnuts may have different effects on postprandial cognitive function compared with the nutrient composition of almonds.

The EFFECT study is not the first to explore a high polyunsaturated fat meal using walnuts in relation to cognitive function. A recent crossover trial investigated the effects of a breakfast containing walnuts on cognitive performance [28]. After consuming the walnut breakfast, improvements to executive function were observed compared to a control meal featuring butter as the primary fat source. The effects on memory were mixed, observing a decrease in recall at 2 hours after the meal, but an increased recall at 6 hours compared to the control. This could be related to the walnuts slowing of gastric emptying, which could result in a delayed response. This design administered cognitive tests at baseline and 2, 4, and 6 hours after breakfast, which differs from the EFFECT study, as postprandial cognitive testing was only completed at hour 5. Furthermore, participants were given a snack before the baseline tests and given a lunch between hours 2 and 4. In the proposed study, participants fasted for baseline cognitive tests and did not consume additional food after the high-calorie breakfast. Additionally, the participants were young, healthy adults, which differs from the older population with SCI in the EFFECT study. Therefore, the proposed study would expand our understanding of postprandial cognitive function.

In addition, walnuts alter the gut microbiota by increasing β-diversity and shifting relative bacterial populations [31,32]. Walnuts are a source of ellagitannins, which are metabolized to form anti-inflammatory urolithins [33-35]. We will look at the relationship between gut microbiota, urolithins, and postprandial cognitive function.

### Strengths and Limitations

The EFFECT study uses a randomized, crossover design with a 4-week washout period between interventions. Thus, a strength of this design is that participants served as their own controls. A total of 4 weeks should be sufficient to prevent any carryover effects from the first intervention. Using a run-in period could be considered a limitation, as a study snack used to acclimate participants to consuming 1 study snack per day would be a deviation from their usual diet. However, the fat profile of the run-in period snack is comparable to the typical American diet. An inherent limitation to studying SCI is the subjective nature of the cognitive impairment, as reliance on a self-report of cognitive issues is necessary. Similarly, adherence to the interventions is partially reliant on self-reported consumption. However, changes in fatty acid profiles in erythrocytes were also used as a measure of adherence.

### Conclusions

With no current dietary recommendations for managing SCI, discovering a food that improves cognitive function in adults with SCI is important. The dietary interventions in this study are modest and only require substituting a study snack for a food already being consumed. Walnuts can be easily incorporated into an individual’s diet, and a total dietary overhaul is not required. Consuming certain fats, or reducing consumption of others, could be an effective, inexpensive way to impact the negative effects of SCI. The EFFECT study will enhance our knowledge of the interplay between cognitive function, dietary fats, and SCI.

## Abbreviations

ALA: α-linolenic acid
DASH: Dietary Approaches to Stop Hypertension
EFFECT: Essential Fats for Enhancing Cognitive Thinking
LA: linoleic acid
LASSO: Least Absolute Shrinkage and Selection Operator
NIHTB-CB: National Institutes of Health Toolbox for the Assessment of Neurological and Behavioral Function Cognitive Battery
OSU: Ohio State University
OTU: operational taxonomic unit
PBMC: peripheral blood mononuclear cell
SCI: subjective cognitive impairment
